**Secondary variables**
The percentage of patients with primary failure and early graft dysfunction. Primary graft failure is defined as the complete absence of liver graft function. The patient will not survive without retransplantation. In the case of early graft dysfunction, patient survival is likely and possible without retransplantation, although morbidity will be greater than in the case of normal function. The following Olthoff criteria are used for its definition (one criterion is enough):Bilirubin ≥10 mg/dL on postoperative day 7.International normalized ratio ≥1.6 on postoperative day 7.Alanine aminotransferase or aspartate aminotransferase >2000 IU/mL in the first 7 postoperative days.Length of stay in the intensive care unit and hospitalization. The number of days spent in the surgical intensive care unit and the total number of days spent in the hospital.Dose and duration of catecholamines from the time of reperfusion.Length of time on mechanical ventilation (hours). Time to extubation of the patient.Vitamin C levels before transplantation and 12 hours after transplantation. Measurements are performed by high-pressure liquid chromatography with an ultraviolet detector.Levels of inflammatory markers (IL-1β, tumor necrosis factor alpha, IL-6, IL-8, and IFN-γ) before and after transplantation as measured by the high-sensitivity enzyme-linked immunosorbent assay technique.Development of postoperative kidney failure (acute kidney injury [AKI]) during the first week. AKI is defined as an increase in serum creatinine (SCr) ≥0.3 mg/dL within 48 hours or an increase in SCr × 1.5 times baseline; known or presumed to have occurred within the previous 7 days.Need for postoperative renal replacement therapy during the first week. Need for any type of renal replacement therapy during the first 7 days after transplantation, regardless of the technique used.Graft and patient survival 30 days after transplantation.

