### Participant Timeline

Patients will be monitored from randomization until day 30 post surgery. The team will collect variables daily through postoperative day 7 and a final visit on postoperative day 30. The research team will closely monitor adverse events, including onset, duration, intensity, progression, and outcome, to assess their relationship to the drug.

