### Analysis

Quantitative variables will be described using mean, median, SD, IQR, 95% CI, and range values. Quantitative data will be presented as absolute and relative frequencies. The significance level in any statistical test will be set at α=.05. Both groups will be assessed to ensure they are balanced in all variables.

A total of 2 populations will be established: one based on intention to treat and the other based on efficacy. The first population will consist of all participants randomized at the start and divided into 2 groups according to the corresponding randomization. The second population will consist of the participants who complete the protocol and end up in the same group in which they were randomized. All analyses will be conducted on both populations; however, the primary analysis will focus on the intention to treat the population. Statistical analyses will be performed using SPSS Statistics.

The comparison between participants who experienced PRS during the intervention will be performed using the chi-square test. Cohort proportions are compared using relative risk with 95% CIs. In a secondary analysis, we will adjust for potentially confounding factors related to the main outcome variable by using a multivariate technique. These factors include variables that showed significant differences (with *P*≤.20) between the control and treatment groups and have been identified as potential confounds. When dealing with binary factors, we will assess the magnitude of association with odds ratios, while for ordinal or quantitative factors, we will use the Spearman correlation coefficient. A binary logistic regression analysis will be conducted to examine the presence of PRS. The control variable (ascorbic acid vs saline) and all variables resulting from the previous univariate analysis will serve as independent variables. The same procedure will be applied to secondary efficacy and safety analyses.

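### The one between-arm procedure stated for secondary outcomes is built for binary data, does not fit 11 of the 17 secondary measures, and makes no planned use of the pre-transplant biomarker values

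*Protocol article*

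**What the plan says.** In the protocol article, the Analysis section gives the primary outcome a test, "The comparison between participants who experienced PRS during the intervention will be performed using the chi-square test", an effect measure, "Cohort proportions are compared using relative risk with 95% CIs", and an adjusted model, "A binary logistic regression analysis will be conducted to examine the presence of PRS". Covariates for that model come from a screen for between-arm differences at P≤.20. The section ends: "The same procedure will be applied to secondary efficacy and safety analyses".

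For quantitative variables it otherwise promises only summary statistics. It also mentions the Spearman coefficient, but for ordinal or quantitative factors in the confounder step, not for comparing the arms on an outcome.

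The Secondary variables textbox mixes binary and quantitative measures. Among the quantitative ones are "Length of time on mechanical ventilation (hours). Time to extubation of the patient" and "Levels of inflammatory markers (IL-1β, tumor necrosis factor alpha, IL-6, IL-8, and IFN-γ) before and after transplantation". Vitamin C is likewise measured before transplantation and again 12 hours after it.

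**The concern.** A chi-square test, a relative risk and a binary logistic model all need a yes/no outcome. Days, hours, doses and concentrations are not yes/no. Followed literally, the closing sentence requires each of them to be cut into two classes, and the article gives no cut-offs. That loses information, and it leaves the cut-points open to choice after the data are seen.

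The plan also collects pre-transplant vitamin C and cytokine values but states no between-arm analysis that uses them. Under the P≤.20 screen such a value could enter a model only if it happened to differ between arms, and then only a logistic model that does not suit a quantitative outcome. In a trial of 70 patients, the baseline of a biomarker is one of the few cheap sources of precision.

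**Working it through.** **Step 1. Count the measures by type** (Secondary variables textbox).

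- Binary: primary graft failure, early graft dysfunction, AKI in the first week, renal replacement therapy in the first week, graft survival at 30 days, patient survival at 30 days. That is 6.
- Quantitative: ICU days, hospital days, catecholamine dose, catecholamine duration, ventilation hours, vitamin C, IL-1β, TNF-α, IL-6, IL-8, IFN-γ. That is 11.
- Total 6 + 11 = 17, so 11 of 17 do not fit. Counted by textbox item instead, 5 of 9 are wholly quantitative.
- With a pre-transplant value: vitamin C and five cytokines, 6 of the 11.

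**Step 2. Inputs for the size of the loss.** From the plan: 35 per arm (Sample Size Calculation) and α = 0.05 (Analysis); a two-sided test is taken. Assumed, because the article gives neither: a normal outcome with SD 1 (for biomarkers, after taking logs) and a pre-post correlation r of 0.3 to 0.7. The plan states no power for any secondary outcome, so there is no figure of its own to reproduce here.

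**Step 3. Reference: post-transplant value only, on the continuous scale.** The difference detectable with 80% power is

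d = (1.960 + 0.842) × √(2/35) = 2.802 × 0.239 = 0.67 SD.

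**Step 4. The same difference after a cut midway between the arm means.**

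- Proportions above the cut: Φ(0.335) = 0.631 and 1 − 0.631 = 0.369; difference 0.262.
- Standard error under no difference: √(2 × 0.5 × 0.5 / 35) = 0.1195.
- Standard error under the difference: √(2 × 0.631 × 0.369 / 35) = 0.1153.
- Power = Φ[(0.262 − 1.960 × 0.1195) / 0.1153] = Φ(0.24) = 0.596, about 60%.

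**Step 5. The same difference with baseline adjustment.** ANCOVA multiplies the residual SD by √(1 − r²), so power = Φ[2.802/√(1 − r²) − 1.960].

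| Assumed r | √(1 − r²) | Power at 0.67 SD | Difference with 80% power |
|---|---|---|---|
| 0.3 | 0.954 | Φ(0.98) = 84% | 0.64 SD |
| 0.5 | 0.866 | Φ(1.27) = 90% | 0.58 SD |
| 0.7 | 0.714 | Φ(1.96) = 98% | 0.48 SD |

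**Step 6. Is the chi-square test itself unsound for the rare binary outcomes?** At assumed event rates of 2%, 5% and 10%, expected events per arm are 35 × rate = 0.7, 1.75 and 3.5, all below the usual rule-of-thumb value of 5. The exact type I error was obtained by summing the binomial probabilities of every 35-versus-35 table that the test rejects at a nominal 5%.

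| Assumed event rate | Uncorrected chi-square | Fisher exact |
|---|---|---|
| 2% | 0.5% | 0.006% |
| 5% | 3.6% | 0.3% |
| 10% | 5.7% | 1.3% |

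The plain chi-square is not materially inflated over this range, and Fisher's test is far more conservative.

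**The case against.** The strongest reply is that the closing sentence is loose rather than wrong. The article nowhere tells anyone to dichotomise. It describes quantitative variables on their own scale, and it ties logistic regression to PRS specifically. The shared procedure could mean the sequence of crude comparison, screening and adjusted model, with suitable methods at each step. A condensed article may also leave detail to a fuller document.

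Part of this stands. Dichotomising is what the sentence implies if followed, not something the plan spells out, and the 60% figure prices that literal reading. But the article does not stay silent and defer. It assigns a procedure, and the only between-arm methods in that procedure are for binary outcomes. The loose reading still leaves no named comparison for 11 measures and no planned use of six baselines.

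Three stronger inferences are tempting and not supported:

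- *That the chi-square is unreliable for rare events and should give way to Fisher's test.* Step 6 shows no material inflation, and the article gives no event rates.
- *That early deaths could reverse the direction of the stay and ventilation results.* This needs deaths that are both frequent enough and unequal between arms, and nothing in the article quantifies either. Nor does the statement "Patients will be monitored from randomization until day 30 post surgery" say that stay is cut off then; the textbox defines hospital stay by the total number of days. This does not justify replacing these outcomes with free-day composites, which would be new endpoints and would coarsen ventilation, now measured in hours.
- *That the secondary outcomes are what would justify a larger trial.* The Sample Size Calculation section ties that purpose to differences in the primary outcome, which is binary and suited to the stated procedure.

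**Conclusion.** The point holds, as a should-fix on secondary outcomes only. The sole between-arm procedure stated does not fit 11 of 17 secondary measures without cut-offs that the article does not give, and pre-transplant vitamin C and cytokine values have no planned role. The count depends only on the textbox and on splitting its compound items.

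The size rests on assumptions. Under normality at 35 per arm, 80% power falls to about 60% with a midpoint split. It rises to 84% to 98% with baseline adjustment for correlations of 0.3 to 0.7. At the low end of that range the gain from the baseline is small. The skewed duration and dose measures need not follow the normal calculation, so for them the figures are a guide only. The analysis of PRS is sound in this respect and needs no change.

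**What to change.** Replace the closing sentence of the Analysis section with three statements, settled before the arms are compared:

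- The chi-square, relative-risk and logistic procedure applies to the binary secondary outcomes.
- Vitamin C and each cytokine are analysed by ANCOVA of the log post-transplant value on arm and log pre-transplant value, reported as a ratio of geometric means with 95% CI.
- Catecholamine dose, catecholamine duration, ventilation hours, ICU days and hospital days are compared on their own scale by a Wilcoxon rank-sum test with a Hodges-Lehmann 95% CI. Deaths by arm are reported alongside, so that a short time that ended in death can be recognised.

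The cost is a little more analysis work. It uses only measurements already planned, adds no endpoint and leaves the primary analysis as it is.

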Vitamin C is safe even in very high doses. Fowler et al [32] conducted a safety study of intravenous ascorbic acid in 24 patients with severe sepsis (low dose 12.5 mg/kg every 6 hours vs high dose 50 mg/kg intravenously every 6 hours). No adverse events were observed. No adverse effects were reported in any of the above studies, including the study by Tanaka et al [28], in which the doses were very high (1.6 g/kg over 24 hours). Metabolism of vitamin C to oxalic acid could theoretically cause calcium oxalate nephropathy. However, this does not seem to be a real problem, as renal toxicity is dose-dependent and has only been reported at very high doses (>40 g/day) [33]. In addition, coadministration of thiamine would reduce the conversion of vitamin C to oxalate. In the study by Marik et al [31], the incidence of renal failure requiring renal replacement therapy was significantly lower in the intervention group (33% vs 10%; *P*=.02).

However, several meta-analyses have been published in recent years with mixed results. In most of them, a reduction in mortality, duration of mechanical ventilation, and hospitalization could not be demonstrated. However, a reduction in the sepsis-related organ failure assessment score and a shorter duration of treatment with vasoactive drugs is a common finding [34-38].

I/R injury plays a pivotal role in the development of graft dysfunction after liver transplantation, and excessive free radical production and massive depletion of endogenous antioxidants are common mechanisms underlying I/R injury. Ascorbic acid is an essential micronutrient involved in the antioxidant response and modulation of apoptosis and inflammation. These properties may, therefore, make it a potential strategy for reducing I/R injuries. In addition, its safety profile, low cost, and ease of administration favor its use in this scenario [39]. As discussed above, we can consider PRS as one of the clinical manifestations of I/R injury. Therefore, if we can prevent or at least attenuate I/R injury, we may be able to reduce the incidence of I/R injury.

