### Sample Size Calculation

The current incidence of PRS at our center is 30%. Assuming a 50% decrease in PRS incidence (from 30% to 15%) with an α risk of 5% and a power of 80%, bilateral testing, and the Fleiss correction with a 10% loss rate, we require 268 participants (134 in each group). Due to the limited number of transplants per year in our center, achieving such a large sample will take 6-8 years. Given that this study will be conducted at a single center, the projected patient enrollment is 35 individuals per year, resulting in a final sample size of 70 participants. To attain 80% power with this sample, it is necessary to achieve a complete elimination of PRS. Although it is unlikely that such a reduction in the incidence of PRS would be achieved, we believe that this is a reasonable number of participants to show differences in the primary outcome that, although not reaching the desired statistical significance, would serve to justify a future multicenter randomized controlled trial. Participants will be randomly assigned to groups using a computer-generated sequence created by SPSS Statistics (SPSS Inc). The computer-generated sequence will allocate 35 participants to the ascorbic acid intervention group and 35 participants to the saline control group. To ensure independence, an unrelated staff member will enroll patients and prepare medication or saline upon arrival.

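### For sparse secondary and safety outcomes, the procedure carried over from the primary gives a p-value that depends on the test chosen and, when one arm of 35 has no events, no interval for the ratio

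*Protocol article*

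**What the plan says.** The article's Analysis section describes one chain of methods for PRS. The test: "The comparison between participants who experienced PRS during the intervention will be performed using the chi-square test". The effect measure: "Cohort proportions are compared using relative risk with 95% CIs". The adjusted model: "A binary logistic regression analysis will be conducted to examine the presence of PRS", with treatment and the variables retained from a univariate screen as covariates. The section closes by extending this chain: "The same procedure will be applied to secondary efficacy and safety analyses". It names no exact test, risk difference or rule for small counts, and does not say whether the chi-square test is continuity-corrected.

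The arms are small: "The computer-generated sequence will allocate 35 participants to the ascorbic acid intervention group and 35 participants to the saline control group". Several binary outcomes in the secondary-variables textbox could be infrequent: primary graft failure, graft loss or death by day 30, and renal replacement, worded as "Need for any type of renal replacement therapy during the first 7 days after transplantation, regardless of the technique used". The Introduction mentions a possible renal harm, "Metabolism of vitamin C to oxalic acid could theoretically cause calcium oxalate nephropathy", and then plays it down. Raised serum creatinine is an exclusion criterion.

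**The concern.** A relative risk on the log scale and a maximum-likelihood odds ratio both need at least one event in each arm. A harm seen only under ascorbic acid is the pattern of most safety interest, and it is the case in which these two estimators return nothing usable. The chi-square test still gives a p-value, but with few events that value rests on a large-sample approximation and can fall on the other side of 0.05 from an exact test. The report would then show counts and a p-value that depends on the test, with no statement of how large an excess risk the data allow.

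This is a method that the article states and extends to safety, so it is more than a detail left out.

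**Working it through.** **Inputs.** 35 per arm (Sample Size Calculation); α = 0.05 and the methods above (Analysis). The article gives no expected rate for any secondary or safety outcome in this population, so there is no figure of its own to reproduce and the rates p below are assumptions.

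**1. What happens with an empty arm.** For a/35 vs b/35, SE(log RR) = √(1/a − 1/35 + 1/b − 1/35). With b = 0 the term 1/b is undefined, so there is no interval. Logistic regression has no finite maximum. For 3/35 vs 0/35 the fitted log odds ratio is 9.2 after 10 iterations, 19.2 after 20 and 34.1 after 35, with standard errors of 33, 4,941 and about 8.9 million.

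**2. How often an arm is empty.** Let z = (1 − p)^35. With the same rate in both arms:

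| Rate p | z | Events in treated arm only, z(1 − z) | At least one empty arm, 2z − z² |
|---|---|---|---|
| 3% | 0.344 | 23% | 57% |
| 5% | 0.166 | 14% | 31% |
| 8% | 0.054 | 5% | 10% |
| 10% | 0.025 | 2.4% | 4.9% |

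If treatment doubles the rate, the chance of events in the treated arm only is z_control × (1 − z_treated):
- 3% to 6%: 0.344 × (1 − 0.115) = 30%
- 5% to 10%: 0.166 × (1 − 0.025) = 16%

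**3. The chi-square test with few events.** With equal arms the expected count per arm is (total events)/2, which is below 5 whenever the total is under 10. With the total distributed Binomial(70, p), that has probability 99.8% at p = 5%, 95% at 8% and 84% at 10%. For k/35 vs 0/35, uncorrected χ² = 70(35k)² / [35² · k · (70 − k)] and the two-sided Fisher p = 2·C(35,k)/C(70,k):

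| Events | χ² | Uncorrected p | Fisher p | Risk difference (Newcombe 95% CI) |
|---|---|---|---|---|
| 3 vs 0 | 3.13 | 0.077 | 0.239 | 8.6 points (−2.8 to 22.4) |
| 4 vs 0 | 4.24 | 0.039 | 0.114 | 11.4 points (−0.6 to 26.0) |
| 5 vs 0 | 5.38 | 0.020 | 0.054 | 14.3 points (1.5 to 29.4) |

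At 4 vs 0 and 5 vs 0 the two tests disagree at 0.05. The Newcombe limits for 3 vs 0 combine the Wilson limits (0.030, 0.224) and (0, 0.099): lower = 0.086 − √[(0.086 − 0.030)² + 0.099²] = −0.028; upper = 0.224.

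**4. Is the chi-square test too liberal?** Summing Bin(a; 35, p) × Bin(b; 35, p) over all tables with p-value ≤ 0.05 gives the actual error rate under a common p. At 3%, 5%, 8% and 10%, uncorrected chi-square rejects 1.4%, 3.6%, 5.5% and 5.7% of the time. Fisher's test rejects under 0.1%, 0.3%, 0.9% and 1.3%. The disagreement in step 3 is therefore largely Fisher's conservatism. Chi-square exceeds 5% only slightly.

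**5. The primary outcome.** At the planning rate of 15% under treatment, the chance of an empty treated arm is 0.85^35 = 0.3%.

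**The case against.** Several points on the other side stand.

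- **Safety is not analysed by these methods alone.** The Analysis section also plans counts and percentages (under a label that appears to mean categorical data), and Participant Timeline provides case-by-case follow-up of adverse events. A 3 vs 0 pattern would be seen. It would still lack a between-arm interval.
- **The chi-square test does not break down with one empty arm.** It returns a p-value, and step 4 shows that its error rate is tolerable. What it lacks is agreement with an exact test near 0.05, and an estimate.
- **A reader might infer that the renal harm itself will go unestimated.** The article does not support that. It gives no rate for AKI or renal replacement in these patients. At the only renal rates it quotes, 10% and 33% in sepsis, a given arm of 35 is empty 2.5% of the time or less. It also regards oxalate nephropathy as unlikely to be a real problem.
- **A reader might infer that the primary analysis is bound to fail**, because the article says "To attain 80% power with this sample, it is necessary to achieve a complete elimination of PRS". An undefined ratio would be certain only if the true treated rate were zero, which the article itself calls unlikely. The power statement is also inexact: for 30% vs 0% with 35 per arm, the normal approximation gives Φ[(0.30·√35 − 1.96·√(2·0.15·0.85)) / √(0.30·0.70)] = Φ(1.71), about 96%.
- **The carry-over sentence is condensed.** It also covers lengths of stay and cytokine levels, to which chi-square cannot apply, so it is not a literal specification for every outcome. A separate analysis plan may already name exact methods. If so, it would depart from this sentence, and the two should agree.

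**Conclusion.** The point holds for sparse binary outcomes. With an empty arm, two of the three named methods give no usable result. With fewer than 10 events in total, the third gives a p-value whose side of 0.05 can depend on the test. The first problem is a real prospect at true rates up to about 5-8%: events in the treated arm only have a chance of about 23% at 3%, 14% at 5% and 5% at 8%. The larger figures of 57%, 31% and 10% count an empty arm on either side or both, so they overstate the chance of the treated-only pattern. All of these rest on assumed rates and on 35 analysed patients per arm. The point does not extend to common AKI, and it matters little for PRS at the planning rates. It is a cheap improvement to the reporting of rare outcomes and does not threaten the trial's main conclusion.

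**What to change.** Amend the carry-over sentence in the Analysis section, or state in the analysis plan before unblinding, that for binary secondary and safety outcomes:

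- counts per arm and the risk difference are reported with a Newcombe or Miettinen-Nurminen 95% CI;
- Fisher's exact test is used when any expected count is below 5;
- the ordinary multivariable logistic model is not fitted to outcomes with sparse or zero cells.

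Report the same risk difference and interval beside the relative risk for PRS, so that a zero count still yields an estimate. A penalised logistic model is an option but is not needed.

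The cost is wording only, on data already planned. There are two downsides. Fisher's test is conservative (step 4), which matters when the aim is to detect harm, so the interval should lead the interpretation. The plan should say so, because at 5 vs 0 the Newcombe interval excludes zero while Fisher's p is 0.054. The score-based interval may also need an added SPSS procedure or another package.
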